### Data management and monitoring

2.13

Before this study, the Data Safety and Monitoring Committee (DSMC), composed of experts in rehabilitation, neurology, ethics, and statistics, will be set up for data management and monitoring. The committee is independent from trial investigators, and has no competing interests. All the researchers involved in data management will be trained. Firstly, 3 assessors will be responsible for acquisition and assessment of patients’ information during the study. After assessors finish the case report forms completely, 2 data collectors will validate the completeness and consistency of the data, and then convert the credible paper data to electronic data. All paper and electronic data related to the study will be safely kept in the Clinical Research Center of Beijing Dongzhimen Hospital. Only the independent statisticians will have access to the final complete data, others who have any questions will be required written requests to the DSMC to get permission.

The DSMC is also in charge of monitoring. Members of the committee will monitor the overall quality and completeness of the data, interview assessors, examine original documents, and make sure that the study is implemented with the principles of this protocol. In case of any changes to the study protocol, the DSMC will submit the written application to the REC to obtain permission. In addition, the monitors will verify that all adverse events will be recorded in the correct format. The DSMC will audit the study through regular interviews and the periodic review will be done every 2 months.

### Statistical analysis

2.14

Statisticians who are independent from the trial will be responsible for the statistical analysis. The SPSS 25.0 (IBM, USA) for Windows (Chicago, IL, USA) will be used. Categorical variables will be presented with frequencies or percentages and continuous variables will be presented as the mean and standard deviation. The analysis will mainly compare efficacy between the intervention group and the control group, including primary and secondary outcomes. Changes in all outcome measurements of before and after the treatment and of the between group will be analyzed. The demographic and clinical characteristics of the 2 groups will be compared at baseline applying unpaired 2 sample *t*-tests (continuous data) and Chi-square analysis (categorical data). Rank sum test will be used when the normal distribution hypothesis is not met. Considering some participants may fail follow-up, we will conduct both intention-to-treat analysis and per-protocol analysis. The intention-to-treat analysis will include all the participants. The missing data will be treated by multiple imputations. The per-protocol analysis will incorporate the participants who follow all the time points outcome measurement and fully comply with the treatment schedule in the intervention group. The statistical significance threshold will be set at 0.05 (2-sided), with 95% confidence intervals.

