### Sample size

2.6

The sample size calculation was based on the medial plantar area. According to previous studies,^[23]^ assuming the medial plantar area is 20.15 in the intervention group and 18.94 in the control group; therefore, the mean difference between 2 groups is 1.21 with standard deviations of 2.12 and 2.46. With a type I error of 5% (α = 0.05) and 90% power (β = 0.10), the estimated required sample size is 76 participants per group based on the formula:$$n=2\left[{\left(\mu_{\alpha }+\mu_{\beta }\right)}^{2}\sigma^{2}\right]/\delta^{2}$$

Considering a 20% dropout rate during the study, 95 patients will be enrolled in each group and the total sample size will be 190.

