### Randomization and allocation concealment

2.7

The stratified block randomization scheme will be applied in this trial. An independent statistician will generate the random allocation sequence using SPSS 25. 0 (IBM, USA). All participants who meet the inclusion criteria will be randomly assigned to an intervention group or control group (95 cases each) at a 1:1 ratio by the computer-generated random sequences. Opaque envelopes will be used to seal generated sequences and submitted to 3 centers. The allocation of eligible participants will be concealed from their caregivers and therapists. The therapists will only take charge of the allocated treatments for patients. Moreover, the allocation will also be concealed to the outcome assessors and data statistical analysts.

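### The trial is sized on levels of plantar area but the analysis text speaks of changes, with no baseline or stratum adjustment stated; a baseline-adjusted linear model would keep the planned power whatever the correlation

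*Protocol article*

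**What the plan says.** **Sample size (protocol article, section 2.6).** Planning rests on group levels: "assuming the medial plantar area is 20.15 in the intervention group and 18.94 in the control group", and "the mean difference between 2 groups is 1.21 with standard deviations of 2.12 and 2.46". The result is "90% power (β = 0.10), the estimated required sample size is 76 participants per group", raised to 95 per group for 20% dropout. The section gives no SD of change and no correlation between baseline and follow-up.

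**Analysis (section 2.14).** The sentence on outcomes is "Changes in all outcome measurements of before and after the treatment and of the between group will be analyzed". It names no test, model or covariate. The unpaired t-test and chi-square test are named for comparing demographic and clinical characteristics at baseline. Directly after that comes "Rank sum test will be used when the normal distribution hypothesis is not met", which does not say whether it covers baseline characteristics only or outcomes too. The section also plans multiple imputation and states: "The statistical significance threshold will be set at 0.05 (2-sided), with 95% confidence intervals".

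**Randomisation (section 2.7).** "The stratified block randomization scheme will be applied in this trial". The strata are not named.

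**Data available (section 2.1, Table 1).** Plantar area is scheduled for all patients at baseline, after 4 weeks of treatment and at follow-up.

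**The concern.** The quantity used for sizing and the quantity named for analysis differ. A change score carries the noise of two measurements. It is more precise than the end value only when those measurements are correlated strongly enough, and the protocol gives nothing from which to judge that. The 90% power therefore does not carry over automatically to the analysis that the text describes.

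Two variables that would help are already in the trial: the baseline value and the stratification factors. Neither appears in the stated comparison. Subtracting baseline is not the same as adjusting for it. Subtraction fixes the slope at 1, and when the true slope is smaller it adds noise.

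There is also a question of fit within section 2.14. If the rank-sum rule reaches the primary outcome, the primary test depends on the data. A rank-sum statistic also has no direct pooling by Rubin's rules over the planned imputations.

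**Working it through.** **1. Inputs.** Difference 1.21, SDs 2.12 and 2.46, 90% power, 20% dropout (section 2.6); two-sided 0.05 (section 2.14). Assumptions, because the protocol does not give them: the correlation r between baseline and end value, and equal baseline and end SDs.

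**2. The plan's own figure.** Mean variance = (2.12² + 2.46²)/2 = 5.273, so SD = 2.296. With the protocol's formula, n = 2 × (1.960 + 1.282)² × 5.273 / 1.21² = 75.69, rounded up to 76. Then 76/0.8 = 95 per group and 190 in total. The figures reproduce, and they do so as a comparison of levels.

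**3. SD under each analysis.**
- End value: 2.296, whatever r is.
- Change score: 2.296 × √(2(1 − r)).
- ANCOVA residual: 2.296 × √(1 − r²).

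The change score matches the end value when 2(1 − r) = 1, that is r = 0.5. The ANCOVA variance is (1 − r²) times that of the end value and (1 + r)/2 times that of the change score. Neither factor exceeds 1, so in large samples ANCOVA is never less precise than either.

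**4. Power at 76 per group.** The noncentrality is 1.21 / (SD × √(2/76)), referred to a noncentral t distribution. For the change score at r = 0.3: SD = 2.296 × √1.4 = 2.717, and noncentrality = 1.21 / (2.717 × 0.1622) = 2.745, which gives power 77.9%.

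| r (assumed) | Change score | ANCOVA | n per group for 90% power, change / ANCOVA |
|---|---|---|---|
| 0 | 62.6% | 89.7% | 152 / 76 |
| 0.3 | 77.9% | 92.3% | 106 / 69 |
| 0.5 | 89.7% | 96.1% | 76 / 57 |
| 0.7 | 98.6% | 99.5% | 46 / 39 |

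The last column uses the protocol's normal formula, under which power at 76 is 90.1% where the t distribution gives 89.7%. At r = 0.3 a change-score analysis would need 106/0.8 = 132.5, so 133 per group and 266 in total.

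A simulation of 4,000 trials per setting gave, for end value / change / ANCOVA: 89.8 / 78.0 / 92.2% at r = 0.3, 89.4 / 89.0 / 95.7% at r = 0.5, and 90.0 / 99.0 / 99.5% at r = 0.7.

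**5. Unequal SDs.** If the baseline SD is k times the end SD, the change variance is (1 + k² − 2rk) times the end variance, and the break-even is r = k/2. With k = 0.8 the threshold is 0.4; with k = 1.2 it is 0.6. The ANCOVA factor (1 − r²) does not depend on k.

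**6. Strata.** Suppose the strata explain a share h of outcome variance (assumed; the strata are unnamed) and are balanced by design. A test that leaves them out has actual alpha 2 × (1 − Φ(1.960/√(1 − h))): 0.044 at h = 5% and 0.028 at h = 20%. Power by the normal formula is 90.7% unadjusted against 91.5% adjusted at h = 5%, and 92.5% against 95.3% at h = 20%. The unadjusted test errs on the conservative side and costs about 1 to 3 points of power.

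**The case against.** The strongest reply is that section 2.14 does not commit to an unadjusted change score. Its sentence on changes is loosely worded, the sentence before it speaks only of comparing efficacy between groups, and end values, change scores or ANCOVA could all be fitted under it. This is a condensed article, and a fuller plan may list covariates. That stands to this extent: the power loss is conditional, and silence on covariates is not a decision against them. It does not remove the mismatch. The one outcome quantity that section 2.14 names is change, and section 2.6 did not size for change.

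A second reply is that contact area probably tracks foot size and initial deformity, so r may well be high, and at r = 0.7 the change score loses about 1 point to ANCOVA. That is fair. It is also an assumption that the protocol does not support with a figure, and ANCOVA makes it unnecessary.

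Several stronger readings are tempting, and the text does not bear them out:
- **That the outcomes will be compared by t-test or rank-sum test.** The t-test is tied to baseline characteristics and the scope of the rank-sum sentence is open. Extending either to outcomes is an inference.
- **That the sample size is wrong or the trial underpowered.** The arithmetic is right, and an end-value comparison has the planned 90% at every r.
- **That leaving out baseline or strata biases the result or inflates type I error.** Randomisation keeps the unadjusted comparison unbiased on average, and omitted strata make the test conservative.
- **That a rank-sum test cannot yield a confidence interval.** A Hodges-Lehmann interval can accompany it. The difficulty is pooling over imputations, and it arises only if the rule covers outcomes.
- **That within-arm changes are planned as evidence of efficacy.** Section 2.14 makes efficacy a between-group comparison, and the Discussion gives before-after changes an explanatory role.

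**Conclusion.** The point holds as an inconsistency between sizing and analysis text that a clear improvement would settle. Sizing on levels and analysing unadjusted changes agree on 90% power only if r is about 0.5 or more, assuming equal SDs. Below that, power falls to 78% at r = 0.3. Across the range shown, ANCOVA stays at or above the planned power to within rounding, and it beats the change score by about 14 points at r = 0.3, 6 at r = 0.5 and 1 at r = 0.7. Against end values it gains nothing at r = 0. At r = 0.5 its confidence interval is 13% narrower (√0.75 = 0.866), and at r = 0.7 it is 29% narrower (√0.51 = 0.714).

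The benefit is precision and protection against chance imbalance in baseline area. The size of the gain rests on r, which the protocol does not give. The change should be made, but it does not call the trial's validity into question.

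**What to change.** In section 2.14, or in the analysis plan, state one primary analysis: a linear model of medial plantar area at the primary time point on treatment, baseline medial plantar area and the randomisation strata, with the strata named. Report the adjusted mean difference with its 95% confidence interval.

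Fit the model in each imputed data set and pool by Rubin's rules. If residuals are non-normal, use robust standard errors rather than a data-driven switch to the rank-sum test for the primary outcome. State that the rank-sum rule applies to baseline characteristics, or say where else it applies.

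The cost is a few sentences of text and one degree of freedom per covariate. The variables are already collected, and neither the sample size nor the data collection changes.

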### Interventions

2.9

The patients will receive fumigation treatment (20 minutes) and standardized modern rehabilitation treatment (30 minutes) every day, once a day, 5 days per week (from Monday to Friday) across 4 weeks.

The intervention group will receive PLD fumigation treatment, while the control group will receive placebo fumigation treatment. An expert panel including 3 qualified therapists from the rehabilitation department and 3 senior doctors from the neurology department will set up the fumigation treatment program. According to the proportion of ancient prescription at 1:1, the main components of PLD are shown in Table 2. All Chinese herbal medicine will be made into granules in advance. Each bag of granules for fumigation treatment contains 240 g. The only difference is that each bag of placebo contains 5% PLD only and 95% dextrin. The components of the PLD granules are produced and packed by Bei Jing Kang Ren Tang Pharmaceutical Co. Ltd. The clinical research coordinators will inspect and ensure that all granules meet required quality standards before the trial. When each fumigation treatment begins, the therapist will obtain one bag of granules from the clinical research coordinator, then mix the granules and 400 ml of boiling water into the fumigation treatment machine (HB3000, Suzhou Hao Bo Medical Equipment Co. Ltd, Jiangsu Province, Taicang City). The medial knee and ankle joints of the affected side will be selected as fumigation sites to relieve the spasm pain of the medial muscle group and the strain pain of the lateral muscle group. Patients need to receive the fumigation treatment under the guidance of the therapists who are responsible for them. Any other fumigation treatment is prohibited during the treatment and follow-up period.

**Table 2 T2:** Main components of penony and licorice decoction in fumigation treatment.

Chinese name	Latin name	Amount (g)
Chinese herbal formula penony and licorice decoction		
Bai Shao	Radix Paeoniae Alba	120
Gan Cao	Radix Glycyrrhizae	120

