All patients in 2 groups will receive the same standardized modern rehabilitation treatment according to the “Chinese Guidelines for Stroke Rehabilitation” (2011 version). The main content of modern rehabilitation techniques is Bobath method and proprioceptive neurodevelopmental facilitation technique, which includes good limb position, muscle strength and joint activity training, knee-ankle joint control training, weight loss gait training, and so on. Five qualified and experienced rehabilitation specialists in 3 trial sites will select and conduct appropriate treatment programs according to the participants’ symptoms. All of them will receive the unified training before the start of the trial. Meanwhile, the patients will stick to the treatment they previously had, and will be given present general treatment if acute exacerbation of stroke occurs during the trial.

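### Read literally, the per-protocol set requires treatment compliance in the intervention arm only, so its between-group comparison is open to selection bias

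*Protocol article*

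**What the plan says.** The Statistical analysis section (2.14) of the protocol article states that "we will conduct both intention-to-treat analysis and per-protocol analysis". The first is defined in one sentence: "The intention-to-treat analysis will include all the participants". The per-protocol set is defined as "participants who follow all the time points outcome measurement and fully comply with the treatment schedule in the intervention group". No matching compliance condition for the control group appears anywhere in the article.

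The Interventions section (2.9) shows that controls also have a schedule to comply with. On fumigation: "The intervention group will receive PLD fumigation treatment, while the control group will receive placebo fumigation treatment". Fumigation and rehabilitation are given to the patients "every day, once a day, 5 days per week (from Monday to Friday) across 4 weeks", with no difference between groups. On rehabilitation: "All patients in 2 groups will receive the same standardized modern rehabilitation treatment".

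The sections on randomization and blinding (2.7 and 2.8) keep therapists, assessors, statisticians and data analysts unaware of the allocation.

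**The concern.** Whether a patient completes a daily treatment schedule is known only after randomization and may be related to prognosis. A per-protocol set always gives up some of the protection of randomization. If both arms pass through the same filter, and the placebo looks and smells like the active product, the selection can be expected to be similar on both sides. If only one arm is filtered, that balance is lost by construction: the compliers of one group are compared with the compliers and non-compliers of the other. The two means can then differ even if PLD fumigation does nothing.

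The design gives no reason for the asymmetry. The control is not a no-treatment arm, so attendance can be counted in the same way in both groups.

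At stake is the per-protocol result. A set built in this way cannot serve as a check on the intention-to-treat result, because agreement or disagreement between the two could come from the filter.

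**Working it through.** **1. Same patient, two arms.** Each arm has 5 days x 4 weeks = 20 scheduled treatment days. Applying the stated rule literally:

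| Patient | PLD arm | Control arm |
|---|---|---|
| All assessments, full compliance | kept | kept |
| All assessments, missed sessions | **removed** | **kept** |
| Missed an assessment | removed | removed |

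Only the middle row differs. The bias therefore depends on patients with complete assessments who missed treatment, not on all non-compliers.

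**2. Blinding.** To apply a filter to the intervention group, one must know which group that is. Statisticians and analysts blinded under 2.7 and 2.8 do not. If someone else made the exclusions, finding non-compliance exclusions in one group only would reveal the allocation. A symmetric rule has neither problem.

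**3. The plan's own figures.** From Sample size (2.6): difference 20.15 - 18.94 = 1.21; SDs 2.12 and 2.46; power 90%. Two-sided 5% is from 2.14.

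- SD = sqrt((2.12² + 2.46²)/2) = sqrt(5.273) = 2.296
- n = 2 x (1.960 + 1.282)² x 5.273 / 1.21² = 75.7, so 76 per group
- 76 / 0.80 = 95 per group, 190 in total

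The stated 76, 95 and 190 are reproduced, so 2.296 and 1.21 are a fair scale for the illustration.

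**4. Size with no treatment effect.** Let p be the share of PLD patients with complete assessments who are not fully compliant, and g their outcome deficit in SDs. The unfiltered arm mean equals the compliers' mean minus p x g x SD, so removing the non-compliers raises it by

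shift = p x g x 2.296.

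The article gives neither p nor g; both are assumptions.

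| p | g | Shift | Share of 1.21 |
|---|---|---|---|
| 0.10 | 0.25 | 0.057 | 5% |
| 0.20 | 0.50 | 0.230 | 19% |
| 0.30 | 0.50 | 0.344 | 28% |
| 0.40 | 0.75 | 0.689 | 57% |

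The first and last rows pair both low and both high values, and mark the outer limits. With g = 0 the shift is zero; with g negative it works against PLD.

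**5. Cross-check with a second model.** Let the outcome have correlation rho with a latent tendency to comply, and let a share c of the PLD arm pass the filter. Then shift = rho x SD x phi(z_c) / c, where z_c is the standard normal quantile at c and phi the normal density. Compare 76c PLD patients with 76 controls, using the same SD throughout (an approximation). Both c and rho are again assumptions.

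| c | Shift, rho 0.1 to 0.5 | Share of 1.21 | Type I error (nominal 5%) |
|---|---|---|---|
| 0.9 | 0.04 to 0.22 | 4-19% | 5.2-9.0% |
| 0.8 | 0.08 to 0.40 | 7-33% | 5.5-17.4% |
| 0.7 | 0.11 to 0.57 | 9-47% | 5.9-28.5% |

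At c = 0.8 and rho = 0.3 the shift is 0.241, close to the 0.230 in step 4. At rho = 0 it is zero. At c = 0.8 and rho = -0.3 it is -0.241. With the same filter in both arms, and equal c and rho, the shift is zero and the error rate returns to 5%.

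**The case against.** **The wording may be a slip.** The phrase could be loose English for compliance with the assigned treatment, and the blinding plan suggests that a one-arm filter was not intended. It could also be read as limiting the whole set to intervention patients, which would leave no between-group comparison. This stands as a caution against assuming a deliberate one-arm filter. It does not rescue the sentence, because each of these readings requires it to be reworded.

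**Controls are not unselected.** A reader might infer that the filtered PLD arm is compared with all controls. The text does not support that: on its natural reading, the requirement for assessments at all time points covers both arms. In addition, the Safety assessment section (2.12) withdraws patients with recurrent stroke or other worsening. They would usually lack later assessments and so leave the set in either arm. This stands, and it narrows the asymmetry to the middle row of the first table. It is also why p above refers to patients with complete assessments.

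**The direction is not shown.** A reader might infer that the rule necessarily favours PLD. That requires compliers to do better. It is plausible, since the schedule includes rehabilitation, but patients who recover quickly might also skip daily sessions, which would reverse the sign. With a weak link (rho = 0.1) the type I error is only 5.2-5.9%.

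**The two analyses are not ranked.** A reader might infer that the per-protocol result could decide the trial, because neither analysis is called primary. Ranking the analysis sets is commonly left to the statistical analysis plan, which is not shown. The article names intention-to-treat first and nowhere says that the per-protocol result decides. The silence is not a finding.

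**Conclusion.** The point holds for the per-protocol set only. As written, 2.14 imposes treatment compliance on one of two arms that share a schedule. The resulting comparison is open to selection bias, and the rule cannot be reconciled with blinded analysis.

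Direction and size are conditional. PLD is favoured only if compliers have better outcomes. The 0.23-0.34 units (19-28% of 1.21) rest on an assumed 20-30% non-compliance among patients with complete assessments and an assumed 0.5 SD deficit. The document gives neither figure, and the outer limits of 5-57% show how far the result depends on them.

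The intention-to-treat analysis and the sample size are untouched. A claim that the trial's main conclusion is biased would go beyond the document. Severity: should be fixed.

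**What to change.** Replace the per-protocol sentence in 2.14 with a symmetric rule, for example:

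*The per-protocol set comprises participants of both groups who have outcome measurements at all time points and who met the pre-set compliance threshold for their assigned fumigation (PLD or placebo) and for the rehabilitation schedule. The same definition applies to both groups, and membership is decided before unblinding.*

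The sponsor should set the threshold and record it before any unblinded data are seen. The definition should cover rehabilitation as well as fumigation, because both belong to the schedule and a patient who misses a visit may miss both.

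The cost is one changed sentence and a smaller per-protocol set, since non-compliant controls now leave too. If full compliance stayed the threshold and non-compliance were the assumed 20-30%, that would be about 76 x 0.20 = 15 to 76 x 0.30 = 23 controls; a less strict threshold would remove fewer from either arm. The planned 76, 95 and 190 do not change.

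### The per-protocol rule demands all 20 sessions with no tolerance and, as worded, filters the intervention arm only

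*Protocol article*

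**What the plan says.** The Statistical analysis section (2.14) of the protocol article plans two analyses. For the first, "The intention-to-treat analysis will include all the participants", with multiple imputation for missing data. The second is a per-protocol analysis of those who "follow all the time points outcome measurement and fully comply with the treatment schedule in the intervention group". The operative words are "fully comply with the treatment schedule".

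The Interventions section (2.9) sets the schedule as "every day, once a day, 5 days per week (from Monday to Friday) across 4 weeks". The article does not print a session count, but 5 per week for 4 weeks is 20.

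The article gives no minimum attendance, no tolerance for missed sessions and no expected attendance rate. It states no compliance condition for the control group, although that group follows the same calendar with placebo fumigation.

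**The concern.** A per-protocol analysis is normally meant to describe the effect in patients who were adequately treated. The wording here raises two problems.

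- **Level of the threshold.** Full compliance with 20 sessions means 20 of 20. A patient with 19 sessions is handled like a patient with none. The set then describes patients who never missed a session, and it may be much smaller than the completer population.
- **One-sided application.** Read as written, intervention patients must have all outcome assessments and full attendance, while control patients need only the outcome assessments. Attendance is observed after randomisation. Selecting on it in one arm compares perfect attenders on active treatment with all completers on placebo, and the contrast can be biased whatever the size of the set.

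At stake are the precision and the fairness of the second of the two planned analyses.

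**Working it through.** **Inputs from the article.** Sample size section (2.6): "the mean difference between 2 groups is 1.21 with standard deviations of 2.12 and 2.46"; α = 0.05; power 90%; "the estimated required sample size is 76 participants per group"; 20% dropout, hence 95 enrolled per group. Statistical analysis section: two-sided testing. The SDs are taken in the order of the means, so 2.12 is the intervention arm and 2.46 the control arm.

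**Step 1: reproduce the plan's own figure.**
- Averaged variance: (2.12² + 2.46²)/2 = (4.4944 + 6.0516)/2 = 5.273, so SD = 2.296.
- n = 2 × (1.960 + 1.282)² × 5.273 / 1.21² = 75.7, rounded up to 76 per group.
- 76/0.80 = 95 per group, 190 in total.
- Power at 76 v 76: SE = √(10.546/76) = 0.3725; Φ(1.21/0.3725 − 1.96) = Φ(1.288) = 0.90.

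The stated 76, 95 and 190 all reproduce.

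**Step 2: share retained by a 20-of-20 rule.** The attendance rate p per session is an assumption, shown over a range. If misses are independent, the share with full attendance is p²⁰. The base is 76 completers per arm (95 × 0.80), because the same rule also requires all outcome assessments.

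**Step 3: power in the resulting set.** Power = Φ(1.21/√(2.12²/n₁ + 2.46²/n₂) − 1.96), using unrounded expected numbers. Either n₂ = 76 (only the intervention arm filtered) or n₂ = n₁ (both filtered). The plan's difference and SDs are assumed to hold in the reduced set.

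| p | Share with 20/20 | Patients of 76 | Power, intervention arm filtered | Power, both arms filtered |
|---|---|---|---|---|
| 0.99 | 82% | 62 | 87% | 84% |
| 0.98 | 67% | 51 | 84% | 76% |
| 0.95 | 36% | 27 | 69% | 49% |
| 0.90 | 12% | 9 | 36% | 20% |

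Full attenders fall below half only when p is under 0.5^(1/20) = 0.966.

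**Step 4: clustered misses.** If misses concentrate in some patients, more patients attend everything. A beta-binomial model with intra-patient correlation 0.2 (also an assumption) gives a share B(a+20, b)/B(a, b), with a = 4p and b = 4(1−p).

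| p | Share with 20/20 | Power, intervention arm filtered | Power, both arms filtered |
|---|---|---|---|
| 0.95 | 68% | 84% | 76% |
| 0.90 | 46% | 75% | 59% |

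**Step 5: a tolerant threshold for comparison.** With independent misses, at least 16 of 20 sessions would be reached by 99.7% of patients at p = 0.95 and by 95.7% at p = 0.90. Power with both arms filtered would be 90% and 89%.

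**The case against.** The strongest reply is that the harm in size and power rests on an attendance rate that the article does not supply. At 98% to 99% attendance, 67% to 82% of completers remain and power is 84% to 87% on the one-arm reading. Independent misses are an unfavourable assumption. Sessions are guided by therapists, recruitment includes inpatient departments, and the Quality control section (2.15) plans measures to improve compliance. All of this stands. A reader might infer that the per-protocol set will be a small minority with little power, but the documents do not show that.

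A second reply is that 90% power was never claimed for this set, and that the intention-to-treat analysis covers everyone. That stands too. A reader might infer that the rule undermines the trial's planned power, and it does not.

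A third is that a condensed article may leave the working definition of compliance to a fuller document. That is fair for details such as make-up sessions. It does not remove the point, because the article states a rule: full compliance, tied to one arm. A later document could soften it only by departing from these words. If the reference to the intervention group is merely loose drafting, the asymmetry disappears, but the 20-of-20 threshold remains and the both-arms figures apply.

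Finally, nothing in the article supports a particular cut-off. That stands, and it is why the cut-off needs its own justification.

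**Conclusion.** The point holds as a minor but concrete defect in how the per-protocol set is defined. Two features follow from the wording alone: a 20-of-20 requirement with no tolerance, and its attachment to the intervention arm without a matching condition for controls. The second can bias the contrast even when few patients are lost. The direction of any bias cannot be told from the documents.

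The numerical loss is conditional. Over 99% down to 90% attendance with independent misses, the retained share runs from 82% to 12%. Power runs from 87% to 36% on the wording as it stands, or from 84% to 20% if both arms are filtered. Losses are smaller if misses cluster. These figures assume 76 completers per arm, equal attendance in both arms where both are filtered, and the plan's difference and SDs.

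Two further inferences are not supported. A reader might conclude that full attenders would be the least ill or most mobile patients, but the article does not link attendance to severity. Nor does it follow that a per-protocol result differing from intention-to-treat would be uninterpretable. It would be less precise and possibly selected, and should be read accordingly.

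**What to change.** In the Statistical analysis section, and for the analysis set only, replace the requirement of full compliance in the intervention group with a pre-specified minimum share of scheduled fumigation sessions. 80% (16 of 20) is one conventional example; the sponsor should choose the cut-off and justify it. Apply the same criterion to both arms and determine membership from session records before unblinding. Keep full attendance, also applied to both arms, as a sensitivity set, and label the per-protocol analysis as supportive of the intention-to-treat analysis.

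The cost is about a sentence of text and a blinded check of session records. The downside is that the set will include some patients with slightly less exposure. Treatment, schedule and sample size do not change.
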